#### 7.1.6 Management of Other Toxicity

If any other grade 3 or 4 toxicity that is not outlined elsewhere in Sections 7.1 develops and is deemed attributable to ZD6474, ZD6474 should be withheld until the toxicity resolves to grade 1 or below. Upon recovery, treatment may resume at a permanent reduced dose. If ZD6474 must be withheld for more than 3 weeks for resolution of toxicity, the patient will be withdrawn from study.

Patients who develop CTCAE grade 3 hypertension may continue on therapy if blood pressure is controlled on antihypertensive medication. If blood pressure cannot be stabilized with increased antihypertensive medication, study treatment must be discontinued and cannot be resumed until blood pressure is controlled to baseline level. Patients with CTCAE grade 4 hypertension should discontinue study treatment and cannot resume therapy until blood pressure is controlled to baseline level. If study treatment must be interrupted for more than 3 weeks to allow for toxicity to resolve, the patient's study participation will be discontinued.

### 7.1.7 Summary of Guidance on the Management of Toxicity for ZD6474

| Toxicity                                                             | ZACTIMA                                                                                                                                                                                                                                                                                                                                                                                                                           |
|----------------------------------------------------------------------|-----------------------------------------------------------------------------------------------------------------------------------------------------------------------------------------------------------------------------------------------------------------------------------------------------------------------------------------------------------------------------------------------------------------------------------|
| QTc value $\geq 550$ msec or prolonged $\geq 100$ msec from baseline | Withhold dose; if QTc recovers to $< 480$ msec or baseline, then reduce dose as per section 3.3.5.1. If QTc does not recover to $< 480$ msec or baseline within 3 weeks, patient will permanently discontinue ZD6474.                                                                                                                                                                                                             |
| QTc value $\geq 500$ msec or prolonged $\geq 60$ msec from baseline  | Continue dosing; repeat ECG (in triplicate) within 48 hours; if repeat ECG meets criteria, withhold dose; then if QTc recovers to $< 480$ msec or baseline, reduce dose as per section 3.3.5.1. If QTc does not recover to $< 480$ msec or baseline within 3 weeks, patient must permanently discontinue treatment with study medication. Or, if the repeat ECG does not meet criteria, patient should continue study medication. |
| Grade 3 or 4 cutaneous                                               | Withhold dose until toxicity has resolved to CTCAE grade 1 or less, then reduce dose as per section 7.1.4. If ZD6474 must be withheld for $> 3$ weeks due to cutaneous toxicity, the patient will be withdrawn from study.                                                                                                                                                                                                        |
| Other grade 3 or 4 toxicity related to ZD6474                        | Withhold dose until toxicity has resolved to CTCAE grade 1 or less, then reduce dose as per section 7.1.6. If study treatment must be interrupted for more than 3 weeks to allow for toxicity to resolve, the patient's study participation will be discontinued.                                                                                                                                                                 |

## 7.2 CETUXIMAB DOSE MODIFICATIONS

### 7.2.1 Management of Infusion Reactions

Infusion reactions should be graded according to allergic reaction/hypersensitivity. Caution must be exercised with every cetuximab infusion, as there were patients who experienced their first severe infusion reaction during later infusions. Severe infusion reactions require the immediate interruption of cetuximab therapy and permanent discontinuation from further treatment. Appropriate medical therapy including epinephrine, corticosteroids, intravenous antihistamines, bronchodilators, and oxygen should be available for use in the treatment of such reactions. Patients should be carefully observed until the complete resolution of all signs and symptoms. In clinical trials, mild to moderate infusion reactions were managed by slowing the infusion rate of cetuximab and by continued use of antihistamine premedications (eg, diphenhydramine) in subsequent doses. If the patient experiences a mild or moderate (Grade 1 or 2) infusion reaction, the **infusion rate** should be permanently reduced by 50%. For grade 1 or 2 reactions manifesting only as delayed drug fever, maintain the cetuximab dose and infusion rate. Consideration should be given to administration of acetaminophen or a nonsteroidal anti-inflammatory drug (NSAID)

prior to the subsequent cetuximab infusion if not contraindicated in subjects. Dose and schedule of these agents is entirely at the investigator's discretion.

Cetuximab should be immediately and permanently discontinued in patients who experience severe (Grade 3 or 4) infusion reactions and will need to be removed from the trial.

#### 7.2.2 Treatment of Isolated Drug Fever

In the event of isolated drug fever, the investigator must use clinical judgment to determine if the fever is related to the study drug or to an infectious etiology. If a patient experiences isolated drug fever, for the next dose, pre treat with acetaminophen or non-steroidal anti-inflammatory agent (investigator discretion), repeat antipyretic dose 6 and 12 hours after cetuximab infusion. The infusion rate will remain unchanged for future doses. If a patient experiences recurrent isolated drug fever following premedication and post-dosing with an appropriate antipyretic, the infusion rate for subsequent dosing should be 50% of previous rate. If fever recurs following infusion rate change, the investigator should assess the patient's level of discomfort with the event and use clinical judgment to determine if the patient should receive further cetuximab.

#### 7.2.3 Management of Pulmonary Toxicity

In the event of acute onset (grade  $\geq 2$ ) or worsening pulmonary symptoms which are not thought to be related to underlying cancer, cetuximab therapy should be interrupted and a prompt investigation of these symptoms should occur. Cetuximab retreatment should not occur until these symptoms have resolved to grade 1. If interstitial lung disease is confirmed, cetuximab should be discontinued and the patient should be treated appropriately and withdrawn from study.

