## 1.8 ADVERSE EVENTS in ZD6474 (ZD6474) Lung Cancer Studies

The most common AEs associated with ZD6474 in the phase I and other monotherapy studies included rash, diarrhea and asymptomatic QTc prolongation. In Study ZD6474IL/0003 (the largest monotherapy ZD6474 study conducted as of this date,) subjects with locally advanced or metastatic (IIIB/IV) non-small cell lung cancer were enrolled after failure of first-line and/or second-line platinum-based chemotherapy. In Part A, subjects were randomized to 1 of 2 double-blind treatment arms; 300 mg ZD6474, or 250 mg gefitinib. The most frequent AEs for ZD6474 (Part

A) were diarrhea (55.4%), fatigue (36.1%), rash (27.7%), and nausea (24.1%). Approximately 10% of subjects who received ZD6474 had an adverse event of hypertension (HTN). The majority were Common Toxicity Criteria (CTC) grade 1 or 2. Three subjects developed CTC grade 3 HTN, and none were CTC grade 4. There were no serious adverse events (SAEs) of HTN. The median increase in systolic blood pressure for subjects who received ZD6474 was 10 mmHg; the median increase in diastolic blood pressure was 6 mmHg.

An increased incidence of SAEs was noted in subjects who received ZD6474 compared to those who received gefitinib (44.6% vs. 35.3%.) Cardiac disorders (6.0% vs. 1.2%), gastrointestinal disorders (6% vs. 2.4% mainly diarrhea,) and respiratory disorders (13.3% vs. 8.2%) did occur more frequently in subjects receiving ZD6474. The cardiac events included a variety of terms without any apparent pattern. Respiratory events were primarily those that would be anticipated in subjects with advanced lung cancer. Three subjects receiving ZD6474 developed pulmonary embolism and 3 subjects developed interstitial lung disease, but cases were confounded by such factors as smoking, reduced mobility, infection, lung cancer progression and previous chemotherapy or radiation therapy. One subject in each arm developed a serious skin disorder. One subject who received ZD6474 developed a hematologic event, as did 2 subjects who received gefitinib. No subjects who received ZD6474 developed serious hepatotoxicity.

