### Toxicities in Humans

Diarrhea and neutropenia are the major dose-limiting toxicities of irinotecan. Diarrhea can occur in two situations, within the first 24 hours and after 2-4 days. In the former situation, diarrhea may be associated with abdominal cramping and is thought to be mediated by non-competitive inhibition of acetyl cholinesterase activity by irinotecan. This is usually readily treatable with atropine, 0.25-1 mg, intravenously.

When diarrhea occurs late (after 2-4 days), and often after the second or third weekly dose of irinotecan, it can be a potentially serious event. In contrast to early diarrhea, delayed diarrhea appears to be secretory in nature and to result from abnormal intestinal ion transport. Anti-diarrheal agents, such as loperamide, diphenoxylate-atropine (Lomotil®), octreotide, scopolamine and bismuth are typically ineffective once grade IV diarrhea has occurred. The diarrhea usually lasts 5-7 days before resolving. Early recognition of diarrhea and prompt institution of an intensive and prolonged course of loperamide appears to be the most effective approach to this problem. It is recommended that patients take 4mg of loperamide immediately after their first loose bowel movement. Loperamide 2mg should be taken every 2 hours for a total of 12 hours if diarrhea persists. If no further loose bowel movements occur, therapy may be discontinued.

Myelosuppression is manifested primarily as leukopenia and neutropenia. Other toxicities include nausea, vomiting, alopecia and cumulative fatigue or asthenia. Instances of possible drug related hepatic toxicity have occurred, but are rare. Further descriptions are found in the package insert for irinotecan.

Several cases of interstitial pneumonitis have been reported, predominantly in the Japanese literature, with an incidence of 1.3%. Most reports have occurred in patients with primary lung tumors, where it is unclear whether the pulmonary toxicity was attributable to irinotecan, to progression of the underlying malignancy or to a combination effect. Clinically, this is manifested as worsening shortness of breath, fever and a reticulonodular infiltrate on CXR. Corticosteroids may be helpful in treatment. Hence, the exact mechanism by which pulmonary toxicity is mediated is unknown; however, a current belief is that it may represent an idiosyncratic reaction to the drug. No characteristic histologic correlates have been identified.

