## 7.1 ZD6474 DOSE MODIFICATIONS

For guidance on the management of QTc prolongation, see Figure 1 below. For all other toxicities, the dose of study treatment will be withheld for up to 3 weeks until the toxicity has resolved to CTCAE grade 1 or better, and then study treatment may be restarted. Patients will be withdrawn from the study if toxicity does not resolve to CTCAE grade 1 or better within 3 weeks. Dose reduction/re-challenge for each toxicity criterion will be managed as discussed in the sections that follow.

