### 7.3.5 Other toxicities

Other toxicities attributable to irinotecan as deemed by the investigator (except alopecia) should be managed as such

| Grade                         | Action                      | Resumption of therapy       |
|--------------------------------------|------------------------------------|------------------------------------|
| Grade 0,1,2 other toxicity           | Continue irinotecan                | No dose reductions                 |
| Grade 3/4 toxicity (except alopecia) | Hold until no greater than grade 2 | Resume with 1 level dose reduction |

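### For acute grade 2 or worse pulmonary symptoms only cetuximab has an explicit hold and restart rule; the texts for ZD6474 and irinotecan conflict, so their handling during the work-up is unclear

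*Protocol*

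**What the plan says.** **Cetuximab.** Section 7.2.3 covers acute-onset grade 2 or higher, or worsening, pulmonary symptoms not thought related to the underlying cancer. In that case "cetuximab therapy should be interrupted and a prompt investigation of these symptoms should occur". On restart: "Cetuximab retreatment should not occur until these symptoms have resolved to grade 1". On outcome: "If interstitial lung disease is confirmed, cetuximab should be discontinued and the patient should be treated appropriately and withdrawn from study".

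**ZD6474.** Section 7.1 has no pulmonary subsection. After sending QTc prolongation to its own figure, it opens with "For all other toxicities, the dose of study treatment will be withheld for up to 3 weeks until the toxicity has resolved to CTCAE grade"; the level required for restart there is grade 1 or lower. Section 7.1.6 sets a narrower trigger: "If any other grade 3 or 4 toxicity that is not outlined elsewhere in Sections 7.1 develops and is deemed attributable to ZD6474", the drug is withheld. The 7.1.7 summary table also uses grade 3 or 4 related to ZD6474. The Alert Page clarification on potassium gives grade 3 as the cut-off for holding ZD6474, as for other toxicities.

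**Irinotecan.** Section 7.3.5 covers other toxicities that the investigator attributes to irinotecan. In its row for "Grade 0,1,2 other toxicity" irinotecan continues without reduction. After grade 3 or 4 it is held until grade 2 or lower. The opening of Section 7.3 instead makes resumption conditional on other irinotecan-related toxicity having fallen to grade 1 or less.

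**DLT window.** The Section 7 introduction keeps patients on assigned doses for the first 28 days (dose level 1) or 35 days (dose levels 2 to 4), unless a DLT is observed or the patient is withdrawn. It applies the modification guidelines to patients with a DLT in that window, or with treatment-related toxicity after it.

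**The concern.** New grade 2 dyspnea in a patient on three drugs is a foreseeable event in this trial. At that point the cause is unknown; that is why 7.2.3 asks for a prompt investigation. The protocol says plainly what to do with cetuximab. For the other two drugs a site must choose between passages that give different answers, and within the DLT window it is unclear whether the cetuximab instruction applies at all.

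The protocol's own ILD and pneumonitis reports concern those other two drugs, and one of them, ZD6474, is the agent being escalated. At stake is whether patients are handled alike, and as intended, between the onset of symptoms and a confirmed diagnosis.

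**Working it through.** The protocol states no figure on this point, so the check is a comparison of texts.

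**1. Grade 2 dyspnea, cause unknown, after day 35 at dose levels 2 to 4**
- Cetuximab: interrupted (7.2.3).
- ZD6474, by the opening of 7.1 read literally: withheld until grade 1 or better, since no triggering grade is named.
- ZD6474, by the Alert Page, 7.1.6 and 7.1.7: the grade 3 cut-off is not met, so no hold is triggered.
- Irinotecan, if the event is attributed to it: continued (7.3.5).
- Irinotecan, if it is not attributed: 7.3.5 does not speak. Whether the term study treatment in 7.1 reaches irinotecan is not stated; the sentence stands under the ZD6474 heading.

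The opening of 7.1 cannot be meant literally for every grade, because 7.1.5 makes no dose modification for grade 1 or 2 diarrhea and 7.1.4 withholds for rash at grade 3. It defers to later sections on dose reduction and re-challenge but says nothing on which grade starts the hold. It therefore does not settle the matter.

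**2. The same event inside the DLT window**
A grade 2 pulmonary event meets none of the DLT criteria in Section 3.2. Under the Section 7 introduction the patient stays on assigned doses, and the modification guidelines are not said to apply. Section 7.2.3 carries no such limit. The two give different answers for cetuximab on, say, day 20.

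**3. Restart**
- Cetuximab: grade 1 (7.2.3).
- ZD6474: grade 1 or below (7.1, 7.1.6, 7.1.7).
- Irinotecan after attributed grade 3 or 4: grade 2 by 7.3.5, grade 1 or less by 7.3. This is a direct conflict.

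**4. What the protocol reports by drug**
- ZD6474 (Section 1.8): "Three subjects receiving ZD6474 developed pulmonary embolism and 3 subjects developed interstitial lung disease", described as confounded. One death is listed as ILD. Seven fatal adverse events are listed for the ZD6474 arm, six of them respiratory.
- Irinotecan (Section 6.2): "Several cases of interstitial pneumonitis have been reported, predominantly in the Japanese literature, with an incidence of 1.3" per cent, with attribution unclear and no deaths reported.
- Cetuximab (Section 6.3 table, 281 patients): dyspnea in 51 (18%), grade 3 or 4 in 20 (7%); no ILD or pneumonitis row.

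**5. Side calculation, on assumptions**
The ZD6474 arm size in the monotherapy study is not printed. Its percentages (55.4, 36.1, 27.7, 24.1, 44.6, 6.0, 13.3, 49.4) all fit N = 83; 166 and 249 also fit. If the three ILD cases belong to that arm:
- 3/83 = 3.6% (exact 95% interval 0.8% to 10.2%)
- 3/166 = 1.8%
- 3/249 = 1.2%

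This only shows that the event is not negligible. The finding does not depend on it.

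**The case against.** The strongest reply is that the protocol manages toxicity drug by drug on purpose. A first grade 3 rash reduces ZD6474 only, nail toxicity reduces cetuximab only, and irinotecan may be held while the others go on. Different thresholds by agent are then a design choice. That stands: a reader might infer that one event must carry the same order for every drug, and nothing in the protocol requires it. What remains is that single drugs carry conflicting instructions.

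A reader might also infer that the protocol orders ZD6474 and irinotecan to continue through grade 2 pulmonary symptoms. It does not. No text orders ZD6474 to continue; absence of a hold follows only from the grade 3 cut-off, against the opening of 7.1. The irinotecan row applies only to toxicity attributed to irinotecan, which a symptom under work-up may not be.

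The safety data can be over-read too. Thirteen adverse events in the monotherapy study had a fatal outcome; if all arose in the two-arm Part A, 13 − 7 = 6 fell in the gefitinib arm, close to balance. The deaths are reported for ZD6474 and none for irinotecan, so they cannot be assigned to both drugs. The cetuximab table lists only the most significant or common events, so a missing ILD row does not show that cetuximab is the wrong drug to hold.

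Finally, there are safeguards. Confirmed ILD leads to withdrawal, and Section 11 lets the investigator remove a patient when it is no longer safe to continue. Accrual closed in May 2010, so the instruction now matters for patients still on treatment. These points limit the consequence; they do not tell a site which passage governs before confirmation.

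**Conclusion.** The point holds as a conflict of instructions. For acute grade 2 or worse pulmonary symptoms, the protocol is explicit for cetuximab only. It gives two readings for ZD6474, is conditional and internally inconsistent for irinotecan, and leaves open whether the cetuximab hold applies inside the DLT window. An amendment is warranted because the uncertainty covers the escalated drug, for which the protocol itself reports ILD and a death listed as ILD.

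No sample size, error rate or MTD rule changes. It may be tempting to add the ZD6474 and irinotecan rates and apply the sum to all 34 patients. The documents do not support that: the rates come from lung cancer or mainly primary lung tumor populations, the ZD6474 rate is at 300 mg with an inferred denominator, dose level 1 has no irinotecan, and 34 is the top of a range of 3 to 34. An effect on the severity recorded at each dose level might also be inferred, but nothing in the protocol shows one.

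The conclusion rests on Section 7 and the Alert Page as printed and on no outside rate.

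**What to change.** Reconcile the Alert Page clarification, the Section 7 introduction, the opening of 7.1, 7.1.6, 7.1.7, 7.2.3, the opening of 7.3, and 7.3.5. The result should be one pulmonary instruction that states, for acute-onset or worsening symptoms not thought due to the cancer:

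- what applies to cetuximab, ZD6474 and irinotecan while the cause is being investigated
- what applies to each after the investigation, including the grade required for restart
- whether the instruction also operates within the 28- or 35-day DLT window

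Cross-reference it from 7.1.7 and 7.3.5. The clinical content, including whether the drugs are handled alike or differently, is for the sponsor and investigators to decide. The cost is a short text amendment with no new tests, visits or staff.

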#### 7.2.4 Management of Dermatologic Toxicity

Patients developing dermatologic toxicities while receiving cetuximab should be monitored for the development of inflammatory or infectious sequelae, and appropriate treatment of these symptoms initiated. Since both ZD6474 and cetuximab can lead to dermatological toxicities, the following schema should be followed required dose reductions:

- \* For the first instance of grade 3, dose-reduce ZD6474 only.
- \* For subsequent instances of grade 3 rash, both ZD6474 and cetuximab should be dose reduced

Dose reductions of cetuximab are permanent; no re-escalation of dose is allowed. Cetuximab cannot be held for more than 3 weeks; if cetuximab is held for more than 3 weeks, the patient will need to be discontinued from the trial. Dose reductions of cetuximab are as follows:

| Grade 3 Rash               | Cetuximab                           | Dose modification                   |
|----------------------------|-------------------------------------|-------------------------------------|
| 1 st occurrence | Hold infusion until grade 1 or less | Continue at 250 mg/m  * |
| 2 nd occurrence | Hold until grade 1 or less          | Reduce to 200 mg/m      |
| 3 rd occurrence | Hold until grade 1 or less          | Reduce to 150 mg/m      |
| 4 th occurrence | Discontinue study treatment         |                                     |

\* ZD6474 will be reduced for first occurrence

#### 7.2.4 Management of Nail Toxicity

Cetuximab may be skipped for up to 3 weeks for severe nail / fingertip cracking. Followed above table (for skin toxicity), though ZD6474 will not be dose reduced at the first instance. Cetuximab will be reduced as in the Table for skin toxicity starting at the row for 2nd occurrence of rash.

### 7.3 Irinotecan Dose Reductions

Treatment with irinotecan can resume if  $ANC \geq 1200/mm^3$ , the platelet count is  $\geq 100,000/mm^3$ , and any other irinotecan-related toxicity resolved to  $\leq$  grade 1. If irinotecan is held for irinotecan-related toxicities that are not attributable to ZD6474 or cetuximab, treatment with cetuximab and ZD6474 may continue. **Irinotecan cannot be delayed for more than 3 weeks or the patient should be removed from protocol therapy.**

